### Safety monitoring and adverse events

2.10

No AEs have been reported with the use of the product till now in various clinical studies conducted earlier in subjects but as a precautionary measure we are monitoring the routine hematological, biochemical, and urine analysis in the in-house laboratory. In addition, the subjects would be asked an open question like “Have you noticed any change in your health since your last visit?” For all AEs, the investigator will pursue and obtain information about the type, severity, date of onset, treatment given, duration, outcome, causality as assessed by WHO criteria, and decide on whether the AE is serious or not. The serious adverse event (SAE) will be recorded on SAE form and reported to the Ethics Committee and to the Sponsor's representative. The sponsor has taken adequate insurance in case of any need for post trial care or compensation to those who suffer from harm as a result of participation in the trial.

## Measures

3

Measures include demographic data, vital signs (including heart rate, blood pressure, weight), etc. The primary and secondary study efficacy outcomes are listed in Table 2 and schedule of enrolment, interventions, and assessments is given in Table 3.

**Table 2 T2:**
[figure not shown]
Primary and secondary study efficacy outcome.

**Table 3 T3:**
[figure not shown]
Schedule of enrolment, interventions, and assessments.

### Restorative Sleep Questionnaire (RSQ-W) total score

3.1

RSQ-W is a validated scale for measuring refreshing quality of sleep. It has 9 items with answers scaled from 1 to 5. Some items are reversed scored. The total score is an average score based on all 9 items and rescaled to a 0 to 100 scale, using the following transformation: RSQ-W Total Score = (RSQ-W average score across completed items – 1) X 25.

### WHOQOL-BREF scores

3.2

WHOQOL-BREF is a 26-item, self-administered, cross-culturally validated questionnaire in which items are rated on a 5-point scale. The 26 items measure the following broad domains: physical health, psychological health, social relationships, and environment. Domain scores are scaled in a positive direction (i.e., higher scores denote higher quality of life). The mean score of items within each domain is used to calculate the domain score. Mean scores are then multiplied by 4. The second transformation method described in the manual converts domain scores to a 0 to 100 scale. The study will use the English version.

### Hospital and Anxiety Scale (HADS) score

3.3

Hospital and Anxiety Scale (HADS) is a 14-item cross culturally validated scale with 7 items each in 2 subscales for evaluation of symptoms of anxiety (HADS-A) and depression (HADS-D). It detects symptoms of anxiety and depression, rather than making a diagnosis of the syndrome, and excludes symptoms that may arise from physical illness, insomnia, or fatigue. Each item is scored (0–3) according to severity, with a maximum possible score of 21 for each subscale. A score of 0 to 7 indicates no anxiety or depression, a score of 8 to 10 indicates a borderline case, and a score of 11+ indicates presence of anxiety and/or depression. The study will be using English version for the study.

### Actigraphy parameters

3.4

Actigraphy is a noninvasive method of monitoring human rest/activity cycles. It is validated against gold standard Nocturnal Polysomnogram. Using software algorithms, sleep parameters such as latency to sleep, sleep duration, awakenings per night, and sleep efficiency are calculated. We will be able to distinguish between 3 groups (pure NIS, pure NRS, and a mixture of both) using actigraphy. Another advantage of actigraphy will be assessment of sleep in subject's own natural environment.

### Nocturnal polysomnography (NPSG) parameters

3.5

Nocturnal polysomnography (NPSG) is considered a gold standard test for objective measurements of sleep parameters such as total bed time, TST, sleep efficiency, SOL, WASO, micro arousal index, % of each sleep stage (NREM stage 1, 2, and 3 and REM), apnea/hypopnea index (AHI), and periodic limb movement index (PLMI). The NPSG monitors many body functions, including brain (EEG), eye movements (EOG), muscle activity or skeletal muscle activation (EMG), and heart rhythm (ECG) during sleep. Recordings will be taken from bedtime to awakening in the morning and continuous audiovisual infra red monitoring of the subjects. Sleep stages shall be manually scored according to guidelines in American Academy of Sleep Medicine (AASM) Manual for the Scoring of sleep and Associated events in 30-second epoch page.

### Serum C-reactive protein levels (CRP)

3.6

Serum CRP, a systemic marker of inflammation, is associated with an increased risk for a host of chronic diseases. Reduction in the CRP level would suggest reduction in chronic inflammation.

### Statistical analysis

3.7

The data will be collected from paper case report forms (manually counter checked with source files by the data entry personnel) by the investigator and given to the statistician who will analyze the data for demographics, efficacy, and safety. Data will be presented as mean ± SD/SE or number (percentage). Descriptive statistics will be used for different variables at baseline. *P* value of < .05 will be considered as statistically significant. Standard statistical tests will be used to analyze the data obtained. For efficacy analysis both, modified intention-to-treat (mITT) analysis and per-protocol (PP) analysis will be done. The PP analysis will be considered as definitive, while the mITT analysis will be considered as supportive during the trial analysis.

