### Study design

2.3

This is a prospective, randomized, double-blind, parallel, placebo-controlled, single-center, clinical study. The study will be conducted at International Institute of Sleep Sciences, Thane, Maharashtra, India. The study protocol (AN-02ASH 0816H3-IIS01 version. 01 dated October 18, 2016) is approved by institutional ethics committees and registered with Clinical Trials Registry- India (www.ctri.nic.in) (CTRI registration number: CTRI/2017/02/007801). The study will be conducted according to the Declaration of Helsinki 2013, the ICH-GCP E6 (R1, R2) 1996, and ICMR-National Ethical Guidelines for Biomedical and Health Research, 2006. The investigational product will be Ashwagandha extract 300 mg in size “0” capsule of M/s Arjuna Natural Extracts Ltd., Aluva, Kerala, India, and matching placebo in size “0” capsule for reference group.

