### Sample size

2.4

Differences of 10 points and 15 points for RSQ-W total score are considered as clinically significant and clinically highly significant, respectively. Assuming standard deviation of 25 points, these differences correspond to standardize effect size of 0.4 (small-to-medium) and 0.6 (medium-to-large), respectively, as per Cohen recommendation. The difference of 10 points for RSQ-W total score (range 0–100 points) also translates to about 1-point change on 5-point Likert scale in 4 of 9 items of the RSQ-W. Similarly, the difference of 15 points for RSQ-W total score translates to about 1-point change in 5 of 9 items of the RSQ-W.

Group-sequential method will be used to determine the sample size. The planned sample size of 150 subjects (75 in each study treatment group) will be required to detect a difference of 10 points in change in RSQ-W total score at 6 weeks from the baseline between the study treatment groups, assuming a standard deviation of 25 points and a 15% drop-out rate, to achieve 80% statistical power at 5% (2-sided) level of significance. Two interim analyses are planned to occur after completion of the study of 50 subjects and 150 subjects. If the analysis turns out to have a statistically nonsignificant difference, then the enrollment may extend to 236 subjects. The final analysis will be performed when all 236 subjects complete the study.

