### Investigational product and dosage

2.7

The investigational product used in this study is a proprietary detoxified root extract of Ashwagandha (*W somnifera*, Solanaceae) and is manufactured by Arjuna Natural Extracts Ltd, Aluva, Kerala, India. Harvested dried roots of Ashwagandha, visually identified by a qualified botanist, are used to manufacture the extract. The extraction solvent used was ethanol: water with a proportion of 70:30 with a raw material to extract ratio of 13:1. The extract was standardized by HPLC to contain 35% glycowithanolides. The analysis of heavy metals was done with ICP-MS and conforms to EU standards (Lead < 0.5 ppm, Arsenic < 1 ppm, Cadmium < 1 ppm, Mercury < 1 ppm). The microbial assay was done using AOAC, BAM method and conforms to EU standards (Yeast/Mould <100 cfu/g, Salmonella Absent/25 g, *Escherichia coli* Absent/10 g). Identically colored and similar sized placebo capsules were used as the placebo.

Ashwagandha extract or matching placebo capsules will be given as two 300 mg capsules once daily in the evening 2 hours before food with water. The dosage of Ashwagandha extract (Shoden) capsules is standardized to contain 21 mg of glycowithanolides per dose. No dose modification will be allowed in the study. Subjects needing concomitant medication will be managed as per the exclusion criteria of the study. Those subjects having adverse events (AEs) that require standard treatments will be discontinued. Investigational product accountability and telephonic follow-up are used to monitor adherence to protocol.

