Ashwagandha's anti-anxiety effects have been evaluated in published literature.^[11]^ It also shows promise for relieving insomnia and stress-induced depression.^[12]^ Ashwagandha can significantly reduce cortisol concentrations and the immunosuppressive effect of stress.^[13]^ It also has shown to have a lowering effect on CRP denoting reduction in pro-inflammatory responses in body.^[10]^ Beyond reducing stress levels, Ashwagandha can improve physical performance and reduce fatigue sensation in both sedentary people and athletes.^[17]^ In fact, Ashwagandha has been shown to improve fatigue score in post-chemotherapy breast cancer subjects.^[14]^

The inclusion criteria were kept broad and the exclusion criteria were considered to protect study participants and increase the chance of finding a treatment effect. The protocol amendments will only be incorporated in mutual agreement between the sponsor and the investigator. The amendments will be submitted to the ethics committee for its approval.

All subjects will be evaluated in their own setting with Actigraphy, thus giving opportunity to examine the changes in real-life scenario. The subjects will be instructed to wear the Actiwatch continuously for a period of 7 days. The noncompliance could be objectively detected by the software algorithms incorporated in the device.

Although compliance will not be formally measured in this study, a regular phone call as well as personal visits to the institute at regular intervals shall be done. Dosage format will be once a day in the evening, which is practical and relevant to the real-life scenario.

The analyses will include all participants regardless of their compliance but will not include dropouts. We will also assess the heterogeneity of treatment effect in several relevant subgroups. The trial results will be communicated through publication in leading journals.

The sample size was calculated to give enough power for study without resorting to crossover design thus avoiding potential chance for certain errors such as carryover effect of the medicine.

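### The per-protocol analysis is made definitive in a placebo-controlled superiority trial and dropouts are left out, so the deciding comparison rests on a set selected after randomisation

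*Protocol article*

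**What the plan says.** Section 3.7 (Statistical analysis) plans two efficacy analyses: "For efficacy analysis both, modified intention-to-treat (mITT) analysis and per-protocol (PP) analysis will be done". It then ranks them: "The PP analysis will be considered as definitive, while the mITT analysis will be considered as supportive during the trial analysis".

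The Discussion describes who is analysed in other terms: "The analyses will include all participants regardless of their compliance but will not include dropouts".

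Two statements bear on adherence. Section 2.7 (Investigational product and dosage) says: "Investigational product accountability and telephonic follow-up are used to monitor adherence to protocol". The Discussion opens a sentence with "Although compliance will not be formally measured in this study" and goes on to mention phone calls and visits. Section 2.7 also gives one route out of the study after randomisation: "Those subjects having adverse events (AEs) that require standard treatments will be discontinued".

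Section 2.3 gives the design: "This is a prospective, randomized, double-blind, parallel, placebo-controlled, single-center, clinical study". Section 2.4 sizes the trial to "detect a difference of 10 points in change in RSQ-W total score at 6 weeks from the baseline between the study treatment groups", with an SD of 25, 15% dropout, 80% power and a two-sided 5% level. Section 2.9 sets efficacy boundaries at 50, 150 and 236 subjects (P of .0002, .012 and .0475) and does not name the analysis set to which they apply.

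**The concern.** In a superiority trial, comparing the groups as randomised is what allows a difference to be attributed to treatment. A per-protocol or completers-only set removes people for what happened after allocation. If the reasons differ between arms and are linked to outcome, the remaining groups are no longer comparable, and a larger sample does not cure this. Giving a per-protocol analysis equal or greater weight is usually argued for in non-inferiority or equivalence trials. The article has no such margin and offers no other justification.

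The sentence in 3.7 decides which result counts as the trial's conclusion. If the two analyses disagree, the plan as written follows the per-protocol result. The Discussion sentence adds a second problem: it describes a set defined by completion and not by compliance, so the article gives two descriptions of the deciding population.

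**Working it through.** **1. Type of question.** The design is randomised against placebo, the target is a 10-point difference, the test is two-sided, early stopping is for efficacy, and no margin is stated. The article does not use the word superiority, but these features amount to it.

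**2. Which set decides.**

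| Reading | Source | Who is left out |
|---|---|---|
| Per-protocol in the usual sense | 3.7 | Subjects with non-adherence, violations or withdrawal |
| Completers regardless of compliance | Discussion | Dropouts |

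The readings differ, but under both of them membership depends on events after randomisation. Discontinuation for certain adverse events (2.7) is one such event that treatment could influence. The planned 15% dropout (2.4) shows that the excluded group is not expected to be negligible.

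**3. The plan's own sample size.** With a difference of 10, SD 25, two-sided 5% and 80% power:
- n per arm = 2 × 25² × (1.96 + 0.8416)² / 10² = 98.1, rounded up to 99.
- Allowing for 15% dropout: 99 / 0.85 = 116.5, rounded up to 117, or 234 in total.

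This agrees with the maximum of 236. With 15% lost (118 × 0.85 = 100.3 per arm), a simulation of the three looks gives 81% power. So 236 is a size for about 100 retained subjects per arm who show the full effect. (150 subjects do not reach 80% on these inputs. That is a separate matter, and nothing here depends on it.)

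**4. What selective exclusion could do (assumed inputs).** Suppose there is no true effect, 15% of each arm is excluded, placebo exclusions are random, and excluded active subjects have a mean change g points worse than those retained. The retained active mean then lies 0.15 × g above the full active-arm mean, so

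bias = 0.15 × g

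SE = 25 × √(2/100.3) = 3.53 at 236 enrolled

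SE = 25 × √(2/63.75) = 4.43 at 150 enrolled

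two-sided error = P(|Z + bias/SE| > 1.96)

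| g (assumed) | Bias, points | Error at 236 | Error at 150 |
|---|---|---|---|
| 0 | 0 | 5.0% | 5.0% |
| 10 | 1.5 | 7.1% | 6.3% |
| 15 | 2.25 | 9.8% | 8.0% |
| 25 | 3.75 | 18.6% | 13.5% |

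At 236, bias/SE for the last three rows is 0.425, 0.637 and 1.062. These are single-test figures at 1.96. With the plan's final P of .0475 (critical value 1.982), the 1.5-point case gives 6.8% and the 3.75-point case 18.0%. A bias of 1.5 points also arises from exclusions of 20% v 10% with excluded subjects 15 points worse in both arms: (0.20 − 0.10) × 15 = 1.5.

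**5. What it costs to keep everyone in.** With 118 per arm, SE = 25 × √(2/118) = 3.25.
- Full 10-point effect in all subjects: 10/3.25 = 3.07; power = Φ(3.07 − 1.98) = 86%.
- Dropouts (15%) with no benefit, an assumption: average difference 0.85 × 10 = 8.5; 8.5/3.25 = 2.61; power = Φ(2.61 − 1.98) = 74%.
- 80% power at 8.5 points, with a fixed two-sided 5% test: 2 × 25² × (1.96 + 0.8416)² / 8.5² = 135.8, or 136 per arm (272 in total).

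**The case against.** The best defence is that this is an article condensing a longer protocol. Membership rules for the analysis sets may stand in that protocol or in an analysis plan that is not shown, so their absence here is no fault. That is accepted. It does not reach the ranking in 3.7, which is stated outright and which a fuller document could reverse only by contradicting it.

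Four stronger readings are tempting, and the article does not support them:

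- **That subjects are selected on adherence.** The article does not define the per-protocol set. Selection on adherence is inferred from the label, and the Discussion points to completers regardless of compliance.
- **That per-protocol results decide the interim looks.** Section 2.9 names no set. Applying the 3.7 ranking there is plausible but remains an inference.
- **That the bias favours the active arm.** Neither direction nor size can be derived from the article. The table follows from assumed inputs, and its first row shows that exclusions unrelated to outcome do no harm.
- **That 2.7 and the Discussion contradict each other on adherence.** Monitoring by accountability and telephone can coexist with having no formal measure of compliance. The wording is in tension and needs reconciling, but it is not a plain contradiction.

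One further objection changes the remedy. The Discussion leaves dropouts out of the analyses in general, so the mITT analysis may omit them too. Exchanging the two labels in 3.7 could therefore leave the same selection in place.

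**Conclusion.** The point stands and should be corrected before any efficacy look. The plan makes a post-randomisation set definitive in a trial whose question is superiority over placebo, gives no justification, and describes that set in two ways. This follows from the text and needs no assumption.

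The possible damage does rest on assumptions. Selective exclusion of 15% of the active arm with outcomes 10 to 25 points worse than those retained, and random exclusion on placebo, would shift the comparison by 1.5 to 3.75 points. At 236 subjects, the nominal 5% error would then be roughly 7% to 19%. The finding is the lost protection of randomisation. It is not a demonstrated bias of any given size or direction.

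**What to change.** 1. In 3.7, make the analysis of all randomised subjects by assigned arm definitive, and the per-protocol analysis supportive with membership fixed before unblinding.
2. In 3.7 or 2.9, state that the same set governs both interim tests and the final efficacy test.
3. In the Discussion, replace the exclusion of dropouts with a statement that they stay in the primary analysis, using their available data and a named missing-data method. If the term mITT is kept, its definition must not remove dropouts.
4. Reconcile 2.7, 3.7 and the Discussion on how adherence is recorded and whether it affects membership of any set.
5. Restate power for the new primary analysis.

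This leaves the rules on stopping treatment unchanged. It goes beyond an edit of wording: a missing-data method must be specified and applied, and the estimate may be smaller. If dropouts have no benefit, the average difference is 8.5 points and single-look power at 236 is about 74%. The sponsor should either state the lower power or reconsider the maximum size.

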## Discussion

4

The quality of sleep is one of the major hurdles that sleep therapists face in today's society. NRS is one of the indicators of poor sleep quality that results in day time fatigue and lethargy.

Ashwagandha (*W somnifera),* also commonly known as Indian ginseng, is a shrub plant belonging to the Solanaceae family. The various plant parts of (e.g., roots, leaves, and berries) of Ashwagandha have been used by traditional Indian Ayurvedic medicine for thousands of years to help with inflammation, sexual issues, nerve tissue damage, stress, anxiety, insomnia, and many other ailments. The major phytochemical constituents reported from Ashwagandha are alkaloids (isopelletierine, anaferine, cuscohygrine, anahygrine, tropine, somnine, sominiferine, withanine, etc), steroidal lactones (withanolides, withaferins), saponins containing an additional acyl group (sitoindoside VII and VIII), withanolides with a glucose at carbon 27 also known as glycol-withanolides (sitoindoside IX and X), and amino acids such as aspartic acid, proline, tyrosine, alanine, glycine, etc.^[16]^ A lot of herbal supplements are commercially available containing majority of alkaloids and small amount of withaferine. The pharmacological activity of such products has been claimed as due to presence of alkaloids and/or withaferine. European Food Safety Authority (EFSA) has categorized some of the alkaloids of Ashwagandha as toxic and harmful.^[17]^ These include anaferine, anahygrine, withanine, sominiferine, somnine, tropine, etc. Apart from alkaloids, withaferine A has also been categorized as cytotoxic lactones by EFSA.^[18]^

The Ashwagandha extract developed by M/s Arjuna Natural Extracts Ltd., Aluva, Kerala, India, removes all of the alkaloids, thus minimizing the toxic and harmful elements and is standardized to contain 35% glycowithanolides.

Ashwagandha's anti-anxiety effects have been evaluated in published literature.^[11]^ It also shows promise for relieving insomnia and stress-induced depression.^[12]^ Ashwagandha can significantly reduce cortisol concentrations and the immunosuppressive effect of stress.^[13]^ It also has shown to have a lowering effect on CRP denoting reduction in pro-inflammatory responses in body.^[10]^ Beyond reducing stress levels, Ashwagandha can improve physical performance and reduce fatigue sensation in both sedentary people and athletes.^[17]^ In fact, Ashwagandha has been shown to improve fatigue score in post-chemotherapy breast cancer subjects.^[14]^

The inclusion criteria were kept broad and the exclusion criteria were considered to protect study participants and increase the chance of finding a treatment effect. The protocol amendments will only be incorporated in mutual agreement between the sponsor and the investigator. The amendments will be submitted to the ethics committee for its approval.

All subjects will be evaluated in their own setting with Actigraphy, thus giving opportunity to examine the changes in real-life scenario. The subjects will be instructed to wear the Actiwatch continuously for a period of 7 days. The noncompliance could be objectively detected by the software algorithms incorporated in the device.

Although compliance will not be formally measured in this study, a regular phone call as well as personal visits to the institute at regular intervals shall be done. Dosage format will be once a day in the evening, which is practical and relevant to the real-life scenario.

The analyses will include all participants regardless of their compliance but will not include dropouts. We will also assess the heterogeneity of treatment effect in several relevant subgroups. The trial results will be communicated through publication in leading journals.

The sample size was calculated to give enough power for study without resorting to crossover design thus avoiding potential chance for certain errors such as carryover effect of the medicine.

The motivation for the trial design was based on the very common occurrence of nonrefreshing sleep (NRS) in society, its resultant, and the lack of high-quality evidence for the efficacy of the commonly used medication. It is anticipated that this study will result in evidence-based treatment of subjects suffering from nonrefreshing sleep. If negative, the results of this study will still be critical for further efforts to elucidate epidemiology, pathophysiology, and new treatment targets for NRS.

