A total of 150 subjects will be enrolled in this clinical trial to compare the efficacy and safety of the test versus reference product. Study duration per subject will be 6 weeks. Block-randomization will be performed by the statistician using a computer-generated program with blocks of varying length. The length of blocks will be unknown to study team except the statistician involved in generating the randomization list. The mechanism of implementation of the allocation sequence will be sealed envelope method. Opaque sealed envelopes are prepared based on the randomization list. Each envelope will be opened in sequence just before the randomization of a subject and will be kept under controlled access of statistician. The principal investigator (PI) will take the informed consent before enrolling the subjects and will take all necessary precautions in protecting the confidentiality of the subjects. The subjects will be identified throughout and after the completion of the study only by the allotted randomization number to protect the confidentiality. The PI delegated pharmacist will dispense the study products. As this study is double blinded, the PI and the subject will be blinded toward the interventions. If a need to know arises in which case knowing the identity of interventions is necessary, the PI will be permitted to unblind the subject. Adequate subject enrollment would be achieved by those visiting the site, educational pamphlets, and by study camps conducted in nearby places. The enrolled subjects would be assigned to either of the 2 study groups (75 in each study group). Subjects will be instructed to take 2 capsules of Ashwagandha extract 300 mg or matching placebo once daily in the evening 2 hours before food with water.

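### Dropouts are excluded from all efficacy analyses, so even the supportive mITT analysis is a completers analysis open to attrition bias

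*Protocol article*

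**What the plan says.** The rule is in Section 4 (Discussion): "The analyses will include all participants regardless of their compliance but will not include dropouts". It carries no qualification and is the only text in the article that says who enters the efficacy analyses.

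Section 3.7 (Statistical analysis) plans two efficacy analyses: "modified intention-to-treat (mITT) analysis and per-protocol (PP) analysis will be done". It ranks them, "The PP analysis will be considered as definitive, while the mITT analysis will be considered as supportive during the trial analysis", but defines neither set.

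Section 2.7 (Investigational product and dosage) says: "Those subjects having adverse events (AEs) that require standard treatments will be discontinued". It does not say whether this means stopping the product or leaving the study, and no section describes assessments after discontinuation.

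Section 2.4 (Sample size) allows for drop-out: "assuming a standard deviation of 25 points and a 15% drop-out rate, to achieve 80% statistical power at 5% (2-sided) level of significance". Section 2.9 counts subjects who discontinue towards the 50- and 150-subject interim triggers.

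**The concern.** Randomisation makes the two groups comparable when they are formed. Removing people for something that happens afterwards keeps that comparability only if leaving is unrelated to both arm and response. Nothing in the article supports that assumption, and Section 2.7 gives a reason to doubt it: an adverse event that needs treatment, which the product may cause or prevent, can decide whether a subject is analysed.

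If subjects who tolerate the product badly also sleep badly and leave, poor outcomes disappear from the active arm and a tolerability problem shows up as better efficacy. Even without that, the estimate describes those who finished six weeks and not those who were randomised.

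Exchanging the roles of PP and mITT would not help. Because the exclusion applies to the analyses generally, the mITT set becomes completers whatever their compliance. The interim efficacy looks would rest on the same selected group. At 15% drop-out, the look at 50 subjects would use about 0.85 × 50 = 42.5 scores and the look at 150 about 0.85 × 150 = 127.5.

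**Working it through.** **Inputs from the article.** Difference 10 points, SD 25, drop-out 15%, power 80%, two-sided 5% (Section 2.4). Sample size 150, extendable to 236 (Sections 2.4 and 2.9). Equal allocation (Section 2.3).

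**What the drop-out allowance does.** Evaluable subjects per arm = 2 × (1.96 + 0.84)² × 25² / 10², which gives 99 after rounding up. Dividing by 0.85 gives 117 per arm, 234 in total, close to the stated 236. With 236 randomised, 0.85 × 236 / 2 = 100.3 per arm are analysed, and power at two-sided 5% is 80.9%. The allowance therefore replaces lost numbers. It restores power and does nothing about bias. (The figure of 150 does not reach 80% power on these inputs. That is a separate matter and this point does not depend on it.)

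**How many subjects the rule removes.** 0.15 × 150 = 22.5; 0.15 × 236 = 35.4.

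**Illustration A: equal drop-out, active-arm dropouts gain nothing over placebo.** Assume placebo dropouts do as well as placebo completers. Then

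difference in all randomised = (1 − d) × completer difference + d × 0 = 0.85 × 10 = 8.5 points.

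**Illustration B: unequal drop-out.** Assume dropouts in either arm improve *s* points less than completers of the same arm. Then

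difference in all randomised = completer difference − *s* × (drop-out on active − drop-out on placebo).

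Each row keeps the average drop-out at 15%. The split and *s* are assumptions, because the article gives no rates by arm.

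| Drop-out, active / placebo | *s* = 5 | *s* = 10 | *s* = 25 |
|---|---|---|---|
| 15% / 15% | 10.0 | 10.0 | 10.0 |
| 20% / 10% | 9.5 | 9.0 | 7.5 |
| 25% / 5% | 9.0 | 8.0 | 5.0 |
| 10% / 20% | 10.5 | 11.0 | 12.5 |

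Entries are the differences in all randomised subjects when completers show 10 points.

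**Effect on false-positive error.** Suppose there is no true difference in all randomised subjects, and bias *b* = *s* × (difference in drop-out). For a single test at 236 randomised, with about 100.3 analysed per arm, SE = 25 × √(2 / 100.3) = 3.53. The two-sided error is 1 − Φ(1.96 − *b*/SE) + Φ(−1.96 − *b*/SE):

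- *b* = 0.5: 5.2%
- *b* = 1.25: 6.4%
- *b* = 2.5: 10.9%
- *b* = 5: 29%

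A *b* of 2.5 corresponds, for example, to 20% versus 10% drop-out with *s* = 25. A *b* of 5 corresponds to 25% versus 5% with *s* = 25.

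**The case against.** The best defence is that the mITT set is undefined. The completers reading comes from one Discussion sentence that follows a paragraph on compliance, and a full protocol or SAP may define the sets and handle missing data. That defence fails because the sentence is a stated rule, not a gap. An analysis plan that included dropouts would contradict the published article.

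Other points stand in part:

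- The 8.5-point figure shows dilution, not false efficacy. If the completer difference were zero, the same formula would return zero. False efficacy needs drop-out that differs by arm or is selected differently, as in Illustration B. With equal drop-out and the same shortfall in both arms, the bias is zero.
- The direction is not fixed. The last row of the table shows that the completer analysis can also understate the effect.
- Section 2.10 says earlier studies of the product reported no adverse events, so the adverse-event route may be small. The plan still expects 15% to drop out, and the rule removes them whatever their reason.
- Discontinuation in Section 2.7 could mean the product only. With no off-treatment assessment described, leaving the study is the natural reading.
- Making PP definitive already removes subjects after randomisation. The present defect is distinct, because it remains if mITT is promoted to primary.

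**Conclusion.** The concern holds and must be fixed. Followed as written, the plan contains no efficacy analysis of all randomised subjects, and about 15% of them (22 of 150, or 35 of 236) are left out of the primary comparison and of its only stated support. This conclusion rests on the wording alone.

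The amount of bias is not established. Under the assumptions above, a 10-point difference in completers could correspond to anything from 5.0 to 12.5 points in all randomised subjects, and to 10 points if dropouts are alike in both arms. Since Section 2.4 treats 10 points as the threshold of clinical significance, shifts of this order could change the interpretation.

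**What to change.** 1. In the Discussion, delete the clause that leaves out dropouts, and define the mITT set in Section 3.7 so that it agrees.
2. Ask every subject who stops study product, for whatever reason, to complete the week-6 RSQ-W in person or by telephone. Section 2.5 already provides for telephone visits. State in Section 2.7 whether discontinuation refers to product or study. The clinical rule itself need not change for this purpose; what matters is that the outcome is still collected.
3. Base the primary analysis, including the interim looks, on all randomised subjects with a baseline score. Handle scores that are still missing by a likelihood-based mixed model or multiple imputation.
4. Add one reference-based or tipping-point sensitivity analysis.

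Step 2 matters most. The assessment schedule (Table 3) is not visible. If RSQ-W is recorded only at baseline and week 6, a mixed model recovers little beyond a baseline-adjusted completers analysis, and scores that were never collected cannot be recovered later.

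**Cost.** One questionnaire contact for each subject who stops, and a little more analysis. The estimate may be somewhat smaller. In Illustration A, a difference of 8.5 points with all 236 observed (118 per arm) has 74.3% power at two-sided 5%, against 80.9% for 10 points in completers.
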